**Methods/Design:**

The proposed multi-center, cluster-randomized controlled trial will be stratified by the baseline prevalence of smoking in schools. Municipalities with fewer than 100,000 inhabitants will be randomly assigned to a control or intervention group. One secondary school will be randomly selected from each municipality. These schools will be randomized to two groups: the students of one will receive any existing educational course regarding smoking, while those of the other school will receive a four-year, class-based curriculum intervention (22 classroom lessons) aimed at reinforcing a smoke-free school policy and encouraging smoking cessation in parents, pupils, and teachers. The intervention will also include annual meetings with parents and efforts to empower adolescents to change the smoking-related attitudes and behaviors in their homes, classrooms and communities.

We will enroll children aged 12-13 years as they enter secondary school during two consecutive school years (to obtain sufficient enrolled subjects). We will follow them for five years, until two years after they leave secondary school. All external evaluators and analysts will be blinded to school allocation.

The aim of this study is to analyze the effectiveness of a complex intervention in reducing the prevalence of smoking in the third year of compulsory secondary education (ESO) and two years after secondary school, when the participants are 14-15 and 17-18 years old, respectively.

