### Study population

The populations of the included municipalities vary from 11,000 and 30,000 inhabitants. The main economic activities of these communities are tourism and farming.

The study participants will consist of all 12-13 year-old students, who enrolled in the first grade of compulsory secondary education (ESO) over two consecutive academic periods (i.e., 2011-12 and 2012-13). The intervention will take place over the four years during which these adolescents are enrolled in ESO. Written informed consent will be obtained from all students and from at least one parent/guardian per student, according to the declaration of Helsinki.

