### Measurements

Table 1 summarizes the study measurements, variables and schedule. The baseline questionnaire will gather data on a given student’s sociodemographic characteristics, environment and tobacco use, and the attitudes of his/her parents and teachers towards smoking. The smoking question was adapted from a previously validated questionnaire for adolescents [12]. Information on tobacco use will be collected through the following question: *Which of the following statements best describes you? (A) I have never tried to smoke; (B) I have tried cigarettes a few times, but I do not smoke now; (C) I currently smoke less than one cigarette per month; (D) I currently smoke at least one cigarette per month, but less than one cigarette per week; (E) I currently smoke at least one cigarette per week; (F) I smoke every day; (G) I used to smoke regularly in the past, but I do not smoke now.*

**Table 1 T1:** Measures, questionnaires and timeline

**Instrument**	**Assessment area**	**Timing of assessment**
Pre-test questionnaire	Baseline prevalence of smoking	Before randomization
Baseline data form	Student smoking behaviors	At baseline
Teacher baseline data form	Teacher smoking behaviors and attitudes towards smoking and prevention	At baseline
Parent baseline data form	Parent smoking behaviors and attitudes towards smoking	At baseline
Smoking prevalence form	Prevalence of smoking among adolescents	After the fourth year of ESO and two years after graduation

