The components of the social-influences model that will integrated into this curriculum include teaching students to identify the social influences that encourage people to start smoking (e.g., tobacco company advertising campaigns, peer pressure), providing information about the harmful effects of smoking, and nurturing refusal skills. The curriculum will include anti-advertising workshops that are designed to sensitize participants to the power of advertising. The intervention will also seek to: debunk false beliefs about tobacco; encourage positive means for coping with emotion, stress and peer pressure; and help students develop interpersonal relationship skills, self-esteem, strategies for accepting rules and limits, critical thinking skills, problem-solving skills, and the ability to recognize risky situations.

The classroom sessions will be given by trained teachers in the intervention components, smoking prevention and Health. It will consist of seven lessons in the first year (ages 12-13), six lessons in the second year (ages 13-14), five lessons in the third year (ages 14-15) and four lessons in the fourth year (ages 15-16) of ESO. All lessons will be age-appropriate and relevant to the students’ curricula. All lessons will include material that students will work on together with their parents.

#### **
*Families*
**

The parents of our participants will meet with the personnel of the study, at least once per year at the beginning of each academic to receive information about the intervention and learn how they can help keep their children from smoking. These meetings will focus on encouraging parents to: have an appropriate attitude towards drug use; recognize situations that constitute a risk for adolescents; establish rules and limits; be sensitive to the role that family plays in tobacco use; and participate in the smoke-free home initiative. At least once per year, a workshop on smoking cessation will be held for the participating families of each municipality.

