### Strategies to ensure implementation of the intervention and avoid loss to follow-up

For the project to be successful, we will need to maintain our collaborations with the schools for at least four years. Therefore, all activities associated with the project must conform to the needs and interests of each school. Specific activities will be designed to promote continuity, including visits by the research team and periodic mailings to each school informing them of the progress of the study and recognizing their crucial role. The importance of the control group in the study will also be emphasized.

The final follow-up evaluation will occur six years after inclusion, when the participants will have left the participating school. At least three telephone contact numbers and the addresses of parents and tutors will be obtained early in the study. If a student is not easily located for the final evaluation, additional efforts will be made to contact them by telephone and letter. Efforts will be made to minimize the rate of loss to follow-up to reduce any possible bias resulting from loss to follow-up and to adequately assess the impact of the intervention.

#### **
*Outcome assessments*
**

The measures, variables, and timeline are summarized in Table 1. The baseline prevalence of smoking in each school will be assessed by an external evaluator who will be blinded to the group (intervention or control) to which the school has been allocated. All outcome assessors and data analysts will also be blinded to school allocation. To evaluate the effectiveness of blinding, these individuals will be asked to choose the arm to which they believe each school was assigned (possible answers: intervention, control, or unknown). Individuals who respond “intervention” or “control group” will be asked to indicate what led to the formation of that belief. The primary outcome measure will be the prevalence of smoking at years three and six from enrollment. This will be assessed by self reports of tobacco consumption, where smokers are defined as those who consume more than one cigarette per week.

#### **
*Statistical analysis*
**

##### 

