We will compare the smoking prevalence of adolescents in each group at 12 months against the usual null hypothesis of no difference between groups. We will use the Chi-squared test, taking into account the “variance inflation factor” of the adolescent cluster and intraclass correlation coefficient. We will also calculate 95% confidence intervals to assess the clinical significance of our intervention. In our multivariate analysis, we will adjust for potential confounders, if any, using a multilevel logistic regression model. We will estimate the relative and absolute risk reductions and the number needed to treat (i.e., the estimated number of adolescents who must be treated with our intervention rather than the existing school interventions for one additional adolescent to be prevented from smoking), which will be calculated as the reciprocal of the difference between the prevalence of adolescent smokers in the intervention and control groups. All estimates will include 95% confidence intervals.

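### The analysis section places the between-group comparison of smoking at 12 months, but the primary outcome is at years three and six, and Table 1 schedules no 12-month measurement

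*Protocol article*

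**What the plan says.** The Analytic strategy section opens its outcome analysis with "We will compare the smoking prevalence of adolescents in each group at 12 months". The comparison is to use a chi-squared test corrected for clustering. A multilevel logistic model, relative and absolute risk reductions, a number needed to treat and confidence intervals follow, none with a time of its own.

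The Outcome assessments section states: "The primary outcome measure will be the prevalence of smoking at years three and six from enrollment". The abstract gives the aim as "reducing the prevalence of smoking in the third year of compulsory secondary education (ESO) and two years after secondary school", at ages 14-15 and 17-18.

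The Sample size section takes 14% as the control prevalence, a figure for pupils aged 14-15 in the third year of ESO.

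In Table 1 (Measurements), the row for smoking prevalence among adolescents gives its timing as "After the fourth year of ESO and two years after graduation".

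On the length of follow-up, the methods say "The final follow-up evaluation will occur six years after inclusion", while the abstract says "We will follow them for five years, until two years after they leave secondary school".

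**The concern.** The sentence that introduces the outcome comparison is the only one in the analysis section to name a time, and that time is neither of the two in the primary outcome. It also disagrees with the aim, with the age behind the planning prevalence and with the measurement schedule. No 12-month outcome is defined anywhere, even as a secondary one.

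This is more than detail left to a later analysis plan. The article states a time, and the time conflicts with its own primary outcome. An analyst who followed the sentence literally would need data that Table 1 does not schedule. The comparison would come early in a four-year programme, in pupils about a year younger than the group on which the sample size was based.

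**Working it through.** No figure in the plan depends on this point, so the check sets the stated times side by side on one clock. I take time zero as entry to the first year of ESO, when pupils are enrolled, and count the end of the k-th school year as about k years.

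| Place in the protocol article | Stated time | Years from enrolment |
|---|---|---|
| Analytic strategy | 12 months | 1, if counted from enrolment |
| Outcome assessments | years three and six | 3 and 6 |
| Abstract, aim | third year of ESO; two years after secondary school | up to 3; 4 + 2 = 6 |
| Sample size | third year of ESO, ages 14-15 | up to 3 |
| Table 1, prevalence form | after fourth year of ESO; two years after graduation | 4; 4 + 2 = 6 |
| Methods, final evaluation | six years after inclusion | 6 |
| Abstract, follow-up | five years, said to reach two years after leaving school | 5 as stated; 4 + 2 = 6 by its own description |

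**Can 12 months be read so that it fits?** The origin of the 12 months is not given.
- From enrolment it is year 1, which is neither 3 nor 6.
- From the end of the intervention it is 4 + 1 = 5, since "The intervention will take place over the four years during which these adolescents are enrolled in ESO". That is again neither 3 nor 6. It equals the abstract's five years, but the abstract identifies that point with two years after school, not one.

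Neither reading meets a primary outcome time or a Table 1 time.

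**How much of the intervention has been given?** The Classroom sessions section and Table 2 give 7, 6, 5 and 4 lessons in the four years, and 7 + 6 + 5 + 4 = 22, which agrees with the stated total.
- End of year one: 7/22 = 32%.
- End of year three: (7 + 6 + 5)/22 = 18/22 = 82%.
- End of year four, and so at year six: 22/22 = 100%.

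**Does changing only the analysis sentence settle it?** It does not.
- Year six has a match in Table 1 (two years after graduation, 4 + 2 = 6).
- Year three has none. The in-school measurement in Table 1 falls after the fourth year of ESO, about a year later.
- The five and six years of follow-up both claim to end two years after school. Counting school years gives 4 + 2 = 6. Subtracting the age bands (12-13 to 17-18) gives 5. The two figures may come from different ways of counting, but the article does not say so.

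**Does the fix disturb the planning assumptions?** It does not. The 14% already refers to the third year of ESO, so naming year three brings the test into line with the sample-size input.

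**The case against.** The strongest reply is that 12 months is a drafting slip. The aim, the primary outcome and the planning prevalence agree on the third year, and the lack of a 12-month measurement in Table 1 makes a deliberate 12-month primary analysis unlikely. This is plausible, and the intended times can largely be recovered from the rest of the article. It does not remove the error. No sentence assigns the test to year three or year six, and the one time given is wrong against the article's own outcome.

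Part of the reply limits what can be claimed. A reader might infer that the primary outcome has no pre-specified analysis, so that the time of the comparison could be chosen after the data are seen. The documents do not support that. The Outcome assessments section fixes the outcome times in advance. The multilevel model, risk reductions and number needed to treat carry no time and can be read with that definition. The method is stated, and only its time label is wrong.

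A reader might also want to put a number on the power lost at 12 months. The article gives no prevalence for that age in these schools. Its Discussion offers only European Union figures of 5% at age 12 and 21% at age 16. Any power figure would rest on a guessed rate, and the contradiction does not need one.

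**Conclusion.** The point holds as a contradiction in the current text. The stated comparison is at 12 months, whereas the primary outcome is at years three and six, the aim and the sample-size basis point to the third year, and Table 1 has no 12-month measurement. Taken literally, the test would come after 7 of 22 lessons and would not address the primary outcome.

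The 7 of 22 assumes that 12 months runs from enrolment at the start of ESO and that lessons follow the yearly plan. The mismatch with years three and six does not depend on that assumption, since counting from the end of the intervention also misses both times.

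Two further mismatches belong to the same correction: Table 1's in-school measurement comes after the fourth year and not at year three, and follow-up is five years in one place and six in another. The finding does not extend to an open choice of time point or to a quantified loss of power.

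**What to change.** In the Analytic strategy section, replace the 12-month time with the primary outcome times, three and six years after enrolment. State that the cluster-adjusted test, the confidence intervals, the relative and absolute risk reductions and the number needed to treat apply at each.

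In the same edit:
- Reconcile Table 1 with the outcome definition, so that a prevalence measurement is scheduled at year three as well as two years after graduation. If the measurement after the fourth year of ESO is also intended, give its role.
- State one length of follow-up in the abstract and the methods, and say from which point the years are counted.

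The cost is one sentence in the analysis section, one row of Table 1 and one phrase on follow-up. No sample-size input changes. If the schedule really contains no year-three survey, one has to be arranged, and that is a practical cost beyond the wording.

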**Sample size** A recent study on smoking in adolescents aged 14-15 years (third year of ESO) found that the prevalence of regular tobacco use in the Balearic Islands was 14% [13]. Using this as the prevalence for our control group and presuming that our intervention will reduce the prevalence of tobacco consumption in the intervention group by at least 40%, the use of 1,002 students per group will yield a statistical power > 80% for our between-group comparisons, assuming a bilateral α error of 5% and a 10% loss of participants to follow-up. The cluster size will be approximately 100 adolescents per municipality; we expect a 0.02 intra-class correlation coefficient [14], yielding a 2.98 cluster design effect. The design effect was calculated using the formula: Deff = 1 + (m – 1) * ICC; where “Deff” corresponds to the design effect, “m” is the cluster size and “ICC” is the intraclass correlation coefficient. The target sample size for each group was calculated to be 1,113 students, or 2,226 students in total. To achieve this sample size, students in the first year of ESO (aged 12-13 years) will be recruited over two consecutive years at 22 schools in the Balearic Islands.

##### 

**Analytic strategy** We will test for significant differences in baseline characteristics between the control and intervention groups. We will perform a descriptive and cluster analysis with continuous variables summarized using means and standard deviations for normal distributions, and by medians and 25^th^ and 75^th^ percentiles for non-normal distributions. All data analyses will involve intention-to-treat populations (i.e., all randomized patients, regardless of participation in any treatment session). This approach will reduce the bias that may occur when participants that fail to receive the assigned treatments are excluded from the analysis. All tests will be two-sided, and α-values of 0.05 will be considered statistically significant.

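### The variance-inflated chi-squared comparison with 22 schools does not assure the two-sided 5% level: depending on where the ICC comes from and on the strata, its size can lie above or below 5%

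*Protocol article*

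**What the plan says.** The Analytic strategy compares smoking prevalence between arms as follows: "We will use the Chi-squared test, taking into account the" variance inflation factor "of the adolescent cluster and intraclass correlation coefficient". It sets the level: "All tests will be two-sided, and α-values of 0.05 will be considered statistically significant". It promises 95% confidence intervals for all estimates, and adds a multilevel logistic model to adjust for potential confounders.

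The Sample size paragraph gives the scale. Students "will be recruited over two consecutive years at 22 schools in the Balearic Islands". "The cluster size will be approximately 100 adolescents per municipality", and "we expect a 0.02 intra-class correlation coefficient [14], yielding a 2.98 cluster design effect".

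The Random assignment section allocates schools within strata of baseline smoking prevalence, and the Limitations section repeats this. The test as described does not use the strata. The article does not say whether the ICC in the inflation factor is estimated from the trial data or taken as 0.02.

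**The concern.** A chi-squared reference on 1 degree of freedom treats the variance of the difference as known. Here the variance is dominated by variation between schools, and 11 schools per arm carry only about 20 degrees of freedom on it. If the ICC is estimated, the reference distribution is too narrow. If the ICC is fixed in advance, the error rate depends on whether the guess was right.

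A second feature works the other way. Stratified randomization balances the arms on whatever the strata explain, but an unstratified test leaves that variance in its denominator, so the test becomes conservative. The declared 5% level and the 95% coverage of the intervals are at stake, and neither the direction nor the size of the error is fixed by the plan.

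**Working it through.** **Inputs from the article.** 22 schools; ICC 0.02; cluster size about 100; control prevalence 14%, with a 40% relative reduction (to 8.4%); 1,002 analysed students per group; two-sided 5%. The design effect reproduces: 1 + (100 − 1) × 0.02 = 2.98.

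**Assumptions.** 11 schools per arm, so 22 − 2 = 20 between-school degrees of freedom. Analysed school size 2 × 1,002 / 22 ≈ 91. The share of between-school variance explained by strata is not given, so it is varied.

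**Statistic.** X² = (pA − pB)² / [p(1 − p)(D/nA + D/nB)], with D = 1 + (m − 1) × ICC, referred to chi-squared on 1 df (|z| > 1.960).

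**1. ICC estimated, strata explain nothing.** The root of X² behaves approximately as t on 20 df:
- P(|t20| > 1.960) = 6.4%.
- Simulation under the null (prevalence 14%, mean size 91, ICC 0.01-0.04, school-size CV 0 to 0.65) gives 6.0-6.9%.
- The t20 critical value is 2.086. An interval built with 1.960 is about 6% too narrow (2.086 / 1.960 = 1.064), with coverage near 93.6%.

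**2. ICC fixed at 0.02, strata explain nothing.** The assumed D is 1 + 90 × 0.02 = 2.80. The effective cut-off is 1.960 / √(true D / 2.80), on the normal scale.

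| True ICC | True D | Ratio | Cut-off | Size by formula | Simulated |
|---|---|---|---|---|---|
| 0.01 | 1.90 | 0.679 | 2.379 | 1.7% | 1.3-1.8% |
| 0.02 | 2.80 | 1.000 | 1.960 | 5.0% | 4.9-5.5% |
| 0.04 | 4.60 | 1.643 | 1.529 | 12.6% | 12-13.5% |

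**3. ICC estimated (true value 0.02), strata explain a share f but are left out of the test.** With arms balanced within strata, the true variance of the difference is proportional to (1 − f) × 0.02 + 0.98/91. The test's own variance is proportional to 0.02 + 0.98/91 = 0.0308. The cut-off is 1.960 / √ratio on t20.

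| f | Ratio | Cut-off | Size by formula | Simulated |
|---|---|---|---|---|
| 0% | 1.000 | 1.960 | 6.4% | 6.0-6.9% |
| 10% | 0.935 | 2.027 | 5.6% | 5.3-5.8% |
| 20% | 0.870 | 2.101 | 4.8% | 4.6-5.1% |
| 30% | 0.805 | 2.184 | 4.1% | 3.9-4.6% |
| 50% | 0.675 | 2.386 | 2.7% | 2.3-3.3% |

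The two effects cancel at f of about 18%.

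**4. Candidate remedies.**
- The same unstratified statistic referred to t20 is right only at f = 0 (4.7-5.5%). It falls to 4.1-4.4% at f = 10% and 1.7-2.4% at f = 50%.
- A regression of school prevalence on arm and stratum (two strata, 19 df, critical value 2.093) gives 4.6-5.2% in every setting run (f 0 to 50%, ICC 0.01 to 0.04).

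**The case against.** The best counter-argument is that the article does not establish an inflated error rate at all. A reader might infer that the 5% level is exceeded and that the intervals under-cover. That needs an estimated ICC and strata that explain almost nothing, and the article states neither. With a correct fixed ICC of 0.02 the size is about 5%. With strata explaining more than about 18% of between-school variance it is below 5%. The 12% figure needs both a fixed ICC and a true value twice the planned one, and the fault there is the ICC, not the chi-squared reference. All of this stands, and it limits the claim to a level that is not assured.

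It can also be said that denominator degrees of freedom and the ICC estimator belong in an analysis plan that is not shown. That holds for the multilevel logistic model: the article names no test or reference distribution for it, so no fault can be charged there. It does not dispose of the main comparison, because the article itself names a chi-squared test and describes it without the strata.

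Finally, the sentence that introduces this test refers to 12 months, while Outcome assessments places the primary outcome at years three and six. The article therefore does not settle that this is the primary test, although no other unadjusted comparison is described.

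**Conclusion.** The point stands as a modest and conditional one: the described test does not assure its declared two-sided 5% level. The plausible sizes are about 6-7% with an estimated ICC and uninformative strata, about 1.5% to 12% with the ICC fixed at 0.02 and a true ICC between 0.01 and 0.04, and about 5% down to 2-3% with an estimated ICC when strata explain 20-50% of between-school variance. The level lands on 5% only if the fixed ICC happens to be right or if two opposing errors happen to cancel.

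These figures rest on 11 schools per arm, about 91 analysed students per school, 14% prevalence and, in the stratified simulations, two strata. The share explained by strata and the true ICC are assumptions. The documents do not support the stronger conclusion that the false-positive rate is above 5%.

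**What to change.** Replace the adjusted chi-squared test with a school-level analysis that includes the randomization strata, for example a regression of school prevalence on arm and stratum. An equivalent stratum-adjusted statistic with the ICC estimated from the trial data would also serve. Refer it to t or F on school-level degrees of freedom: 22 − 2, less one for each stratum beyond the first (19 with two strata). Use the same t-based multiplier for the 95% intervals. If the multilevel logistic model is used for inference, state a matching small-sample correction to its degrees of freedom. Changing only the reference to F(1,20), or removing stratum degrees of freedom while the strata stay out of the statistic, is not enough, because the test then becomes conservative whenever the strata matter.

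The change takes a sentence or two and no extra data. In simulation at 14% against 8.4% with ICC 0.02 and variable school sizes, nominal power falls from about 67% to 63% when strata explain nothing. Part of that 67% was bought by a size above 5%. The loss shrinks to almost nothing when strata explain half of the between-school variance.

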### Random assignment

Once informed consent and the commitment to participate have been obtained from the students/parents and the school, respectively, a baseline survey will be performed to determine the prevalence of smoking. Thereafter, the participating schools will be subjected to stratified randomization according to the baseline prevalence of tobacco use at each school by the “random” module, and the option separate strata of PEPI (version 4.0, Sagebrush Press).

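### The only stated between-group test leaves out the baseline-prevalence strata used to randomise schools, and adjustment is conditional; if the strata predict smoking, the test is conservative and loses power

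*Protocol article*

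**What the plan says.** Under Random assignment, "the participating schools will be subjected to stratified randomization according to the baseline prevalence of tobacco use at each school". Design and environment repeats the stratification, and Limitations gives its purpose as comparability of the two groups.

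Under Statistical analysis (Analytic strategy), the comparison of smoking prevalence reads "We will use the Chi-squared test, taking into account the" variance inflation factor and the intraclass correlation. The strata are not mentioned anywhere in the analysis text. Adjustment follows in one clause: "we will adjust for potential confounders, if any, using a multilevel logistic regression model". No covariate is named. The same section opens with "We will test for significant differences in baseline characteristics between the control and intervention groups".

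Baseline smoking is collected for every pupil, and baseline prevalence for every school before randomisation (Measurements, Table 1).

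**The concern.** A factor used to stratify the randomisation belongs in the analysis because of the design, whether or not it later looks like a confounder. Stratification balances the part of the between-school variance that the stratum explains. A variance inflation factor built on the full intraclass correlation still charges the test for that part, so the standard error is too large.

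The proviso on confounders works against the design. Stratification makes baseline prevalence look balanced, so a rule that adjusts only where confounding is seen will tend to omit the one covariate that the design calls for. Leaving the set unnamed and conditional also leaves the adjusted result open to choice after the data are seen.

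Significance tests of baseline differences between randomised groups do not help, because under proper randomisation any difference is due to chance.

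At stake are precision and power in a trial of 22 schools. There is no bias and no excess of false positives.

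**Working it through.** **Inputs from Sample size.** Control prevalence: "the prevalence of regular tobacco use in the Balearic Islands was 14" per cent. Effect: "reduce the prevalence of tobacco consumption in the intervention group by at least 40" per cent, so 14% against 8.4%, a difference of 0.056. Two-sided alpha 5%, ICC 0.02, cluster size about 100, 22 schools (11 per arm assumed from the equal groups), 1,002 analysed and 1,113 recruited per group.

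**The plan's own figures.** The design effect reproduces: 1 + 99 × 0.02 = 2.98. So does the loss step: 1,002/0.9 = 1,113. The 1,002 does not. The usual two-proportion formula at 80% power gives 497 per group; 497 × 2.98 = 1,481, and 1,481/0.9 = 1,646. Power at 1,002 per group is about 63%. That is a separate matter, used here only as the starting point.

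**Starting point at analysis.** Pupils per school m = 1,002/11 = 91. Design effect = 1 + 90.09 × 0.02 = 2.80. Effective n = 1,002/2.80 = 358. SE0 = √[(0.14 × 0.86 + 0.084 × 0.916)/358] = 0.0235. Power = Φ(0.056/0.0235 − 1.96) ≈ 66%.

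**Effect of the stratum (normal approximation).** Variance of a school mean = 0.02 × 0.1204 + 0.98 × 0.1204/91 = 0.00241 + 0.00130. If the stratum alone explains a share r of the first term (assumed; no figure in the document):

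- ratio = [0.00241(1 − r) + 0.00130]/0.00371, and SE1 = SE0 × √ratio
- true size of the unadjusted test = 2[1 − Φ(1.96/√ratio)]
- unadjusted power = Φ[(0.056 − 1.96 SE0)/SE1]
- adjusted power = Φ(0.056/SE1 − 1.96)

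| Share r | Ratio | Size, unadjusted | Power, unadjusted | Power, adjusted |
|---|---|---|---|---|
| 10% | 0.935 | 4.3% | 67.0% | 69.3% |
| 30% | 0.805 | 2.9% | 68.2% | 75.7% |
| 50% | 0.675 | 1.7% | 69.7% | 82.7% |

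The gains are about 2, 8 and 13 points. The unadjusted interval is too wide by 1/√ratio: about 3, 11 and 22%.

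**Small-sample check.** Simulation of 11 schools per arm, 91 pupils each, two strata of 11 schools (the number of strata is not given), t reference with 20 df unadjusted and 19 df adjusted, 20,000 runs. The control arm holds six of the 11 high-prevalence schools.

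| Share r | Size, unadjusted / adjusted | Power, unadjusted / adjusted |
|---|---|---|
| 0% | 4.6% / 4.7% | 62.5% / 61.9% |
| 25% | 3.2% / 4.6% | 69.2% / 69.4% |
| 50% | 2.2% / 5.0% | 72.3% / 77.8% |
| 75% | 0.9% / 4.7% | 77.6% / 88.4% |

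This arrangement flatters the unadjusted test. The extra high-prevalence control school adds to the crude difference (√(0.02 × 0.1204 r) + √(0.02 × 0.0769 r))/11, which is 0.4 points at r = 25% and 0.6 points at 50%. I re-ran it with the odd school in either arm equally often (100,000 runs for each arrangement). Power was then 62.8% unadjusted against 69.9% adjusted at 25%, and 62.7% against 78.6% at 50%. The gains of about nil and 5 to 6 points are therefore the cautious end; averaged over both arrangements they are about 7 and 16.

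**The case against.** The strongest reply is that this is a condensed article. Covariate lists and the handling of strata usually sit in an analysis plan, and nothing here bars the strata from the multilevel model. That stands as far as the missing list goes. It does not cover what the article does state: a test corrected for clustering only, and adjustment that depends on confounders being present.

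The 50% scenario may also be generous. The Discussion puts regular smoking in the European Union at 5% at age 12, and nothing shows how well school prevalence at that age predicts prevalence years later. As an illustration, take ICC 0.02 and 50 to 100 pupils surveyed per school. The reliability of a school's baseline prevalence is then 50 × 0.02/1.98 = 0.51 to 100 × 0.02/2.98 = 0.67. A median split keeps about 2/π of that, so 32 to 43% at most. This limits the likely gain from a two-level stratum. It does not remove the point.

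Four stronger readings are tempting, and the document does not support them:

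- A reader might infer that the baseline tests select the covariates. The two statements are in separate paragraphs and no rule links them.
- A reader might call the chi-squared test the primary analysis. The article does not label it so; it is only the sole between-group test of the null hypothesis that is stated.
- A reader might compare adjusted power with the 66% starting point. That figure assumes that the stratum explains nothing; like for like, unadjusted power rises too.
- A reader might credit the size figures to stratum and pupil baseline smoking together. Only variance balanced by the stratified randomisation makes the unadjusted test conservative. What pupil smoking explains beyond the stratum is not balanced by design.

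**Conclusion.** The point holds as a matter of efficiency and pre-specification. Followed as written, the analysis gives a conservative test and over-wide intervals whenever the stratum is prognostic. Type I error is not inflated.

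The size rests on an assumed share of between-school variance. Normal-approximation gains run from about 2 to 13 points for shares of 10 to 50%. Small-sample gains at 25% run from about nil to 7 points, depending on where the odd school falls. If the stratum predicts nothing, adjustment costs under one point (62.5% against 61.9%). The case for a fixed covariate set does not depend on that share. The loss matters more because the document's own inputs give about 63 to 66% power rather than the figure above 80% that it states.

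**What to change.** Base the main comparison on the multilevel logistic model already planned, or an equivalent cluster-level analysis. Always include the randomisation stratum (or school baseline prevalence) and pupil baseline smoking as pre-specified covariates, and name any others in advance. Delete the proviso on confounders.

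State a small-sample correction for 22 clusters. A normal reference where 20 df apply has a size of about 6.4%, since 2[1 − T20(1.96)] = 0.064, and would exchange a conservative error for an anti-conservative one.

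Keep the cluster-corrected chi-squared test as a supporting analysis. Describe baseline balance without significance tests.

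The cost is wording only: the data are already collected and the model is already planned. The statistical price is about one degree of freedom per stratum term, with a negligible loss of power if the stratum is not prognostic.
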